## Abstract

**Background:**

Colorectal cancer (CRC) is the fourth most common cancer in the United Kingdom. The five-year survival rate from CRC is only 10% when discovered at a late stage, but can exceed 90% if diagnosed early. Symptoms related to CRC can be non-specific, and therefore the decision to refer for a colonoscopy can be challenging. Breath analysis potentially offers a simple and quick method to detect CRC specific volatile organic compounds (VOCs) in breath. This protocol describes the COBRA2 study which aims to develop and validate the clinical prediction model (CPM) in the detection of CRC based on the breath test. An exploratory comparison between the breath test and faecal immunochemical test (FIT) will also be carried out to assess whether combining both tests improves diagnostic performance.

**Methods:**

The COBRA2 study is a multicentre, case-control development and validation study. Breath samples will be collected from participants attending hospital for a planned colonoscopy (control group) or from participants with histologically confirmed colorectal adenocarcinoma (CRC group). A total of 720 participants (470 controls, 250 CRC) will be recruited. All participants will maintain a clear fluid diet for a minimum of 4–6 h prior to sampling, which will take place at outpatient clinics to avoid bowel preparation. The FIT result will be recorded where available. Breath samples will be analysed using gas chromatography–mass spectrometry to identify the VOCs present. Relationships between VOCs of interest and presence of CRC will be explored, and the CPM will be developed using statistical and machine learning methods. We will also assess whether incorporating FIT into the CPM improves diagnostic performance. The CPM will be subsequently validated in an independent sample of up to 250 participants (125 controls, 125 CRC) using the same case–control design and the potential clinical utility of decision rules for triaging will be assessed. If successful, broad validation in an unselected target population of symptomatic patients is required.

**Discussion:**

The non-invasive breath test may provide direct patient benefit through earlier and accurate detection of CRC, and higher patient acceptability. It can help ensure timely secondary care referral, potentially translating to improved curative treatment and survival for patients.

**Trial registration:**

The study is registered with ClinicalTrials.gov (NCT05844514).

**Supplementary Information:**

The online version contains supplementary material available at 10.1186/s12885-025-14520-2.

## Background

In the United Kingdom (UK), colorectal cancer (CRC) is the second most common cause of cancer death, with survival rates amongst the lowest in Europe [1]. If diagnosed early at stage one, the five-year survival is over 90% [2]. However, 23% of patients are diagnosed with advanced disease (stage four) which has a five-year survival of only 10% [3]. Most CRC patients present via the suspected lower gastrointestinal (GI) cancer (30%) or routine (34%) referral pathways, the latter often being associated with significant delay. Twenty-four percent of patients present as an emergency, typically with advanced disease [4].

Early-stage CRC shares many symptoms with common benign conditions and so it can be unclear which patients should be referred for a colonoscopy. Referring all symptomatic patients would overwhelm available resources with demand expected to continue to rise further over the next five years. Annually 1.43 million lower GI endoscopies are performed in the UK, but the diagnostic yield for CRC is lower than 3% [5, 6]. The annual cost of lower Gl endoscopies to the National Health Service (NHS) is estimated to be over £530 million [7]. To improve precision in the early detection of CRC, it is essential to refer patients for colonoscopy who are most likely to have CRC, while not subjecting those at lower risk to an invasive and costly procedure. Therefore, we need sensitive diagnostic tools in primary care that are accurate, easy to perform and accepted by patients.

In the UK, guidelines including the National Institute for Health and Care Excellence (NICE), have recommended the use of the faecal immunochemical test (FIT), which measures the amount of haemoglobin in a stool sample, to triage low-risk symptoms in primary care [8]. Faecal haemoglobin concentrations are known to vary by age, sex, ethnicity, deprivation, cancer stage and iron-deficiency anaemia [9]. Depending on the selected threshold for positivity, sensitivity of FIT for CRC varies between 54 and 93%, specificity between 83 and 95%, with a positive predictive value of 7% in patients with low-risk symptoms [10].

Breath testing is based on the detection of volatile organic compounds (VOCs). VOCs are carbon-containing molecules that are sufficiently volatile to be detectable in a gas form at room temperature [11]. We now know that endogenous VOCs exist as the by- or end-product of biochemical reactions and metabolic processes taking place inside all humans, both healthy and diseased [12]. The non-invasive breath test has the ideal characteristics for a primary care triage tool as it is simple and acceptable to patients of all ethnicities and socioeconomic groups [13], thereby helping to promote equity of healthcare access and optimise patient compliance. There is the opportunity to combine tests based on VOCs with FIT to further enhance performance [14]. In addition, the breath test has the potential as a platform technology to identify other malignant diseases, such as oesophageal, gastric and pancreatic cancers, with different VOC signatures [15, 16]. A primary care clinician faced with non-specific GI symptoms could therefore test for multiple GI cancers from a single breath sample.

Currently, there is limited published data which has assessed the performance of breath VOCs in the detection of CRC [17–23]. In these studies, the performance of VOC-based tests was similar to those of existing stool-based immunohistochemical and DNA tests [24]. However, the potential impact of these studies was limited by sample size, unstandardised methods lacking validation and the non-human origin of some reported VOC markers. In 2022, we completed a discovery study, COlorectal BReath Analysis 1 (COBRA1), which showed the proposed breath test has the potential to detect CRC [25]. A diagnostic model to detect CRC was developed from 855 symptomatic patients (709 controls, 146 CRC) with an area under the receiver operating characteristic (AUROC) curve (± standard error) of 0.91 ± 0.01, sensitivity of 83 ± 2%, specificity of 88 ± 1% and negative predictive value of 96%. This was based on a panel of 14 VOC biomarkers (along with body mass index) identified for CRC. COBRA1 had some limitations that should be acknowledged. This includes heterogeneity of populations and variable use of colonoscopy bowel preparation amongst participants included in the study (although this was not found to be a predictive feature or confounding factor in the VOC-based model). Participants were not sampled if they were receiving any concurrent chemotherapy, but they were not excluded if they had any prior chemotherapy, radiotherapy, or immunotherapy. In addition, the technology was not available at the time to perform robust structural and chemical validation of the VOCs using two-dimensional gas chromatography.

### COBRA2 study objectives

The objectives of the COBRA2 study are to develop and validate a clinical prediction model (CPM), using an improved technology and methodology, to triage the risk of CRC based on profiles of VOCs obtained from the breath test. The clinical utility of the model for referral for the appropriate reference test will be investigated and compared against the current protocol of referring all patients presenting with symptoms indicative of CRC. We will also perform an exploratory comparison between the breath test and FIT, and assess the performance of combining both tests to detect CRC. This will be followed by a narrow validation study using the same case–control design, to assess the ability of the CPM to distinguish between CRC and non-cancer, and to assess the potential clinical utility of decision rules when used for triaging.

We anticipate an improvement in biomarker identification and quantification due to the use of: (i) updated breath collection device and time-of-flight (TOF) and two-dimensional gas chromatography-mass spectrometry (GC–MS) technology; (ii) calibration curves for target compounds; (iii) avoidance of colonoscopy bowel preparation as a possible confounder, and (iv) additional quality control (QC) steps for biomonitoring thermal desorption (TD) tubes, GC-TOF–MS analysis, and a dedicated laboratory environment, therefore enhancing the lower limits of VOC quantification.

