### Sample size

We have powered our study on sensitivity given the poor prognosis of CRC and the clinical importance of minimising missed diagnoses. The sample size calculation aimed to estimate sensitivity and specificity to acceptable precision using a one-sided Binomial test against a fixed target sensitivity. This was implemented using the R package pwr [26]. Sample size was explored for target sensitivities of 85% to 95% and specificities of 80% to 90%, based on the results from the COBRA1 study. For a target sensitivity of 90%, a sample of 200 CRC cases yields 90% power for the lower (one-sided) 95% confidence interval (CI) limit to be ≥ 83%. For a target specificity of 85%, based on the published specificity for FIT at 10 µg/g, a sample size of 262 controls provides 90% power for the lower limit of the 95% CI to be ≥ 78%. Additional controls (total 376) are included to allow assessment of heterogeneity. Reliable and complete data is therefore required in 576 patients (376 controls, 200 CRC). To account for 20% attrition (e.g., incomplete colonoscopy or breath data), we will recruit a total of 720 patients (470 controls and 250 CRC cases) for CPM development. This sample size allows us to estimate the AUROC with a standard error of less than 2% provided it is at least 0.8, and provides acceptable power for estimating other performance measures. Sample size estimation is consistent with methods suggested by Riley et al. [27] for development of diagnostic models. In the narrow validation study, we aim to recruit an equal number of CRC cases and controls, and similarly allow for a 20% attrition rate. The calculated sample size of up to 250 patients (125 controls, 125 CRC), based on the target sensitivity and specificity (85% to 90%), will ensure sufficient precision in estimating diagnostic accuracy (standard errors for sensitivity and specificity 3.5% to 5%), discrimination (standard error for AUROC < 3%), and calibration (standard error for observed/expected cases < 7.5%), whilst maintaining feasibility [28].

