### Statistical analysis

The COBRA2 study is a development and narrow validation study which follows the validation strategy described by Cowley et al. [30] and Transparent Reporting of a multivariable prediction model for Individual Prognosis Or Diagnosis (TRIPOD) guidelines [31]. This method ensures the development of a rigorous and robust CPM that maximises the potential benefit on patient care and decision-making in clinical practice. For development and validation, we use a case–control design for efficiency given that CRC has a low prevalence in the population. Patients referred on the suspected lower GI cancer pathway have a CRC risk of approximately 5–7% [32]. We will use statistical methods for model development and validation. Initially, we will confirm previously identified VOCs using enhanced measurement methods. Using VOCs from COBRA1 as a base, a screening step will identify the most promising additional predictors. Then logistic regression methods will be used to develop a model based on the breath test alone, including all identified VOCs. To reduce over-fitting, we will use model reduction methods such as the elastic net, least absolute shrinkage and selection operator (LASSO) or Harrell’s stepdown approach [33]. For internal model validation, the following will be used [33, 34]:10-fold cross-validation and median values of the performance measures across folds.For calibration, predicted risks of CRC will be plotted against the observed risks.For overall predictive performance Mean Absolute Prediction Error will be estimated (0%: perfect prediction, 100%: no predictive value).For discrimination, the non-parametric AUROC will be calculated, and the threshold that achieves the best trade-off between sensitivity and specificity will be extracted.

For final models, we will use logistic regression modelling to also include patient and clinical characteristics. We will assess linearity of relationships between CRC risk and continuous variables, and explore categorical variables and two-way interactions, including interactions with the breath test. All candidate predictors will initially be entered into the model, before simplification based on Wald statistics (significance < 0.05), size of the predictive weight (odds ratio) and clinical opinion. If there are missing patient or clinical characteristics, we will consider using imputation techniques [35].

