In addition to the statistical methods, random forest and deep neural networks (DNNs) will be explored to assess whether they can improve model predictions. Random forest will be used to construct multiple decision trees from data subsets and combine their predictions to identify key VOCs that predict CRC. DNNs will be employed to model nonlinear relationships in the VOC data. Data analysis and data cleaning will be carried out using the statistical computing language R [36]. We will also calculate the sensitivity, specificity and AUROC of the FIT results (where available). We will compare these quantities informally since there will not be sufficient power for a statistical comparison. We will then assess whether incorporating FIT into the final CPM improves diagnostic performance.

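### The breath-versus-FIT comparison of sensitivity and specificity sets no common operating point, so an apparent difference partly reflects the choice of cut-offs

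*Protocol article*

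**What the plan says.** The COBRA2 study objectives section calls the comparison exploratory: "We will also perform an exploratory comparison between the breath test and FIT, and assess the performance of combining both tests to detect CRC". The method is in the Statistical analysis section, in two places.

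- **Breath model.** In the list of internal-validation measures, next to the non-parametric AUROC: "the threshold that achieves the best trade-off between sensitivity and specificity will be extracted". No other cut-off rule for the breath model appears in the article.
- **FIT.** Later in the same section: "We will also calculate the sensitivity, specificity and AUROC of the FIT results (where available). We will compare these quantities informally". The reason given for the informal approach is lack of power.

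No FIT positivity threshold is stated for this analysis. The only FIT threshold named anywhere is in the Sample size section, where it supports a target for the breath test: "For a target specificity of 85%, based on the published specificity for FIT at 10 µg/g". The Background section reports how far FIT accuracy moves: "Depending on the selected threshold for positivity, sensitivity of FIT for CRC varies between 54 and 93%, specificity between 83 and 95" (per cent).

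**The concern.** Sensitivity and specificity describe one point on a ROC curve. Moving the cut-off trades one for the other without making the test better or worse. If two tests are read at points with different specificities, their difference in sensitivity has two parts: the distance between the curves, and the distance along a curve between the chosen points. Only the first says which test is better.

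The FIT range quoted in the Background section, 39 points in sensitivity (93 − 54) and 12 in specificity (95 − 83), shows that the second part need not be small. Naming a FIT threshold would make the comparison reproducible, but would not by itself remove the problem, because the breath model would still be read at a point chosen by a different rule.

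At stake is how a stated objective will be read. The Sample size section gives priority to sensitivity because of missed diagnoses. With no formal test planned, readers will rely on the side-by-side figures.

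**Working it through.** **What the plan's own figures cover.** The article gives no sample size, power or expected difference for breath against FIT. Its accuracy targets do reproduce, using the one-sample arcsine method with one-sided 5% and 90% power: n = ((1.645 + 1.282)/h)², where h = 2·asin√p₁ − 2·asin√p₀. For 90% against 83% this gives 200.9 (the plan has 200), and for 85% against 78% it gives 261.4 (the plan has 262). These figures concern the breath test against fixed values and do not bear on the comparison with FIT.

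**Inputs for the illustration.**

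- AUROC 0.91 for both tests. This is the COBRA1 breath value (Background); giving FIT the same value is an assumption, made so that the true difference is zero.
- FIT specificity of 83% to 95% (Background), with 85% as the published value at 10 µg/g (Sample size).
- Equal-variance binormal ROC curves (assumption).
- Best trade-off taken as the point that maximises sensitivity plus specificity (assumption; the article does not define it).

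**Formulas.**

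- Separation: d = √2 · Φ⁻¹(AUROC) = 1.414 × 1.341 = 1.896.
- Best trade-off: sensitivity = specificity = Φ(d/2) = Φ(0.948) = 82.8%.
- Sensitivity at specificity s: Φ(d − Φ⁻¹(s)).

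**Two tests on the same curve** (gaps from unrounded values):

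| FIT read at specificity | FIT sensitivity | Breath at best trade-off | Apparent gap (points) |
|---|---|---|---|
| 83% | 82.7% | 82.8% | 0.2 |
| 85% | 80.5% | 82.8% | 2.3 |
| 90% | 73.1% | 82.8% | 9.8 |
| 95% | 59.9% | 82.8% | 22.9 |

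Read at the same specificity, the gap is zero by construction.

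**How far this depends on the assumptions.**

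- With FIT at 95% specificity, the gap is 33.9 points if both AUROCs are 0.85, 18.1 at 0.93 and 12.5 at 0.95.
- With AUROC 0.91 and a ROC slope b between 0.5 and 1.4 (sensitivity at false-positive rate f equal to Φ(a + b·Φ⁻¹(f)), with a = Φ⁻¹(0.91)·√(1 + b²)), the gap at 95% specificity runs from 3.5 to 37.5 points. At 85% specificity it runs from −5.1 to 7.3.
- The sign can change. With both AUROCs at 0.95 and FIT at 83% specificity, breath would look 3.7 points less sensitive (87.8% against 91.5%).

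**Check against COBRA1.** The equal-variance curve with AUROC 0.91 gives 76.5% sensitivity at 88% specificity, whereas COBRA1 reported 83% at 88%. The curve is therefore a device to show the mechanism and does not describe the breath test's actual ROC.

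**The case against.** Several points on the other side are fair.

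- **The cut-offs to be used are partly inferred.** A reader might infer that FIT will be read at 10 µg/g. The article does not say so: that value supports a sample-size target. Nor does it say outright that the trade-off cut-off, listed under internal validation, is the one set against FIT. An analysis plan that is not shown may settle both. It stands, however, that the article describes a side-by-side comparison of cut-off-dependent quantities and mentions no matching.
- **The large figures are extremes.** A reader might take 23 points as the size of the bias. It needs FIT at 95% specificity, which the article never links to this analysis. At the article's own FIT anchor of 85% the gap is about 2 points. That anchor is a planning value, though, and fixes neither the breath cut-off nor the FIT specificity that will be observed.
- **The FIT spread may not come from the threshold alone.** The Background section also says faecal haemoglobin varies with age, sex, stage and other factors.
- **The display contains safeguards.** A reader might infer that the better test would be declared the worse one. The sensitivity ranking can reverse: breath with AUROC 0.88 at its best trade-off reads 79.7%, against 73.1% for FIT with AUROC 0.91 at 90% specificity. At a common 90% specificity, breath would read 64.8%. But the specificities (79.7% and 90%) and the AUROCs would appear alongside, and AUROC would rank the tests correctly.
- **The consequence is limited.** The comparison is exploratory and informal, and broad validation is to follow.
- **The combined model.** A reader might extend the point to breath plus FIT against FIT alone. The article asks only whether adding FIT improves the final model, so that extension is not in the text.

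These points reduce the size and the consequence. They do not make sensitivities read at different specificities comparable.

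**Conclusion.** The point holds in a limited form. Two of the three quantities to be compared depend on the cut-off, the only breath rule stated is the best trade-off, and no common operating point is set. A difference in sensitivity or specificity will therefore partly reflect cut-off choice. On equal-variance binormal curves with AUROC 0.91 for both tests, the spurious sensitivity difference is about 2, 10 and 23 points for FIT at 85%, 90% and 95% specificity. These values depend on the assumed curve and on a FIT operating point that the article leaves open. The AUROC comparison is unaffected, and nothing in the primary development or validation of the breath model is touched. This is a worthwhile and inexpensive improvement to an exploratory analysis.

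**What to change.** Keep the AUROC comparison. In the patients with both a breath result and a FIT result, add two comparisons:

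1. State a FIT threshold for the analysis (for example 10 µg/g, the only value the article mentions). Take the specificity FIT achieves there, and report breath-model sensitivity at that same specificity.
2. Take the sensitivity FIT achieves at that threshold, and report breath-model specificity at that same sensitivity.

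Give each difference with a paired bootstrap 95% CI. Resample patients with both results kept together, and repeat the cut-off selection in every resample. Figures at each test's own cut-off can stay as descriptive results.

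The cost is a few sentences in the analysis plan and a few lines of code on data already being collected, with no extra patients or procedures. Reading off a matched cut-off adds some sampling error, so the intervals will be slightly wider, which is acceptable in a comparison already labelled exploratory.

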## Methods

### Study design

COBRA2 is a multicentre, case–control development and validation study. The study involves collection of breath at a single time point from eligible participants and is open to all NHS trusts. The COBRA2 study is sponsored by Imperial College London and has obtained NIHR Clinical Research Network portfolio adoption to support study recruitment. The COBRA2 study commenced in September 2022 and is due to complete by December 2026.

The following groups of participants are being recruited:i)Control group: symptomatic patients who are attending a planned colonoscopy referred under the suspected lower GI cancer pathway. Any patient who is found to have histologically-proven CRC on colonoscopy will be analysed as part of the CRC group.ii)CRC group: patients who either have a confirmed diagnosis of colorectal adenocarcinoma according to a biopsy, or who are due to undergo surgical resection for suspected CRC (with histological confirmation to follow within three months).

The target recruitment for the development of the CPM is 720 patients (470 controls, 250 CRC), aiming for a total of 576 patients (376 controls, 200 CRC) with reliable and complete data (breath test and reference test). For the narrow validation, the target recruitment is up to 250 patients (125 controls, 125 CRC), aiming for 200 patients (100 controls, 100 CRC) with reliable and complete data.

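### The step from 470 to 376 controls (and 125 to 100) allows for attrition only, although 5–7% of the control stream is expected to be analysed as cases; evaluable controls come to about 350–357 and 93–95

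*Protocol article*

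**What the plan says.** Study design defines the control group by how patients arrive: symptomatic patients on the suspected lower GI cancer pathway who are due a colonoscopy. Participant enrolment confirms that they are found through booking systems and give breath before any endoscopy. Study design then adds the transfer rule: "Any patient who is found to have histologically-proven CRC on colonoscopy will be analysed as part of the CRC group".

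The targets follow in the same section. Development is to recruit 470 controls and 250 CRC patients, and the evaluable goal is put this way: "aiming for a total of 576 patients (376 controls, 200 CRC) with reliable and complete data (breath test and reference test"). Validation is to recruit at most 125 in each group, with a matching goal: "aiming for 200 patients (100 controls, 100 CRC) with reliable and complete data".

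Sample size gives the link between recruited and evaluable numbers: "To account for 20% attrition (e.g., incomplete colonoscopy or breath data), we will recruit a total of 720 patients". It sets 262 controls as the number needed for specificity and adds further controls, to 376, so that heterogeneity can be assessed. It repeats the requirement: "Reliable and complete data is therefore required in 576 patients (376 controls, 200 CRC").

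Statistical analysis supplies the risk, 5–7%, in the sentence that begins "Patients referred on the suspected lower GI cancer pathway have a CRC risk of approximately".

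**The concern.** These statements do not fit together. If controls are recruited before diagnosis, and 5–7% of such patients have CRC, then some of the 470 will be analysed as cases. A patient who changes group has a complete colonoscopy and may have a complete breath sample, so is not attrition of the kind the article describes. The planned number of evaluable controls should therefore be reduced twice, once for incomplete data and once for transfers. Only the first reduction has been made.

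What is at stake is whether the printed evaluable sizes and case-control mix are what the recruitment targets will deliver. If sites close the control stream at 470, the stated 376 would not be expected.

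**Working it through.** **Inputs, all from the protocol article.** Recruited: 470 controls and 250 CRC in development; 125 and 125 in validation (Study design). Attrition: 20% in both groups (Sample size). CRC risk on the control pathway: 5–7% (Statistical analysis). Controls needed for specificity: 262 (Sample size).

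**1. Reproduce the plan's figures.** Evaluable = recruited × (1 − 0.20).
- 470 × 0.8 = 376
- 250 × 0.8 = 200
- 125 × 0.8 = 100

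All are exact, so attrition alone accounts for the whole step.

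The base sizes also reproduce with the arcsine one-proportion formula, n = ((1.645 + 1.282)/h)², where h = 2·asin√p₁ − 2·asin√p₀.
- 90% against 83%: h = 0.2065, n = 200.9 (stated 200)
- 85% against 78%: h = 0.1810, n = 261.4 (stated 262)

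**2. Apply the transfer rule.** Evaluable controls = recruited × 0.8 × (1 − r). Cases gained = recruited × 0.8 × r.

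| | Stated | r = 5% | r = 7% |
|---|---|---|---|
| Development controls | 376 | 357.2 | 349.7 |
| Cases gained | – | 18.8 | 26.3 |
| Development cases | 200 | 218.8 | 226.3 |
| Development total | 576 | 576 | 576 |
| Validation controls | 100 | 95 | 93 |
| Validation cases | 100 | 105 | 107 |
| Validation total | 200 | 200 | 200 |

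The result scales directly with the risk. At an illustrative 3%, evaluable controls would be 364.7 and 97.

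**3. Effect on the stated criteria.**
- Specificity power, Φ(h√n − 1.645) with h = 0.1810: 96.9% at 376 controls; 96.2% at 357; 95.9% at 350.
- Sensitivity power, same formula with h = 0.2065: 89.9% at 200 cases; 92.1% at 219; 92.8% at 226.
- Validation standard error of specificity at 85%, √(0.85 × 0.15/n): 3.57% at 100; 3.66% at 95; 3.70% at 93. The stated range is 3.5–5%.
- Validation standard error of observed/expected, taking the usual approximation √((1 − φ)/(Nφ)) with N = 200 and φ the case fraction: 7.07% at 100 cases; 6.73% at 105; 6.59% at 107. The stated limit is 7.5%.
- Standard error of the AUROC at 0.85 (Hanley–McNeil): development 1.84% at the stated sizes, 1.75–1.77% after transfer; validation 2.75%, then 2.70–2.72%.

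**4. Where the loss falls.** Extra controls above the specificity requirement: 376 − 262 = 114 as stated. After transfer: 357 − 262 = 95 and 350 − 262 = 88. That is 19–26 fewer, or 17–23% of the margin.

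**The case against.** Three counter-arguments deserve an answer.

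**The targets may be counted by final diagnosis.** The transfer rule stands just before the targets, and Sample size speaks of controls and CRC cases as if already classified. On that reading there is no shortfall. The article does not say so, however, and the reading fits poorly: the 470 must include patients lost to incomplete colonoscopy, who have no final diagnosis. If it is what was meant, one sentence settles the matter.

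**The 20% may already cover transfers.** The attrition examples are not an exhaustive list, so this is not strictly excluded. But transferred patients stay in the analysis, and the same 20% is applied to the CRC group, where this transfer cannot happen. If transfers were included, only 1 − 0.8/0.95 = 15.8% to 1 − 0.8/0.93 = 14.0% would remain for incomplete data among controls, and the stated 200 cases would still omit the patients gained.

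**Nothing important is harmed.** This largely stands. A reader might infer that the study loses power for specificity, or that validation calibration suffers because the 1:1 mix shifts. The figures do not support either: specificity power remains about 96%, and the observed/expected standard error gets smaller. Nor does the article attach any power or precision target to the heterogeneity controls.

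A reader might also infer that quotas should be moved from multidisciplinary meetings to the colonoscopy pathway within the 720. That would make the 200 cases depend on incidental cancers. With 505 pathway and 215 meeting recruits and a true risk of 5%, evaluable cases would be 0.8 × 215 + 0.8 × 505 × 0.05 = 192. The present quotas secure 200 after attrition whatever the incidental yield.

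**Conclusion.** The point holds as a correction of stated numbers, and it is minor. On the article's own transfer rule, risk and attrition, the expected evaluable controls are about 350–357 rather than 376, and 93–95 rather than 100. Cases are correspondingly 219–226 and 105–107, and the totals are unchanged. The shortfall in controls is 5–7%. It costs 19–26 of the 114 extra controls and the exact equal split in validation, and it causes no stated power or precision criterion to be missed.

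This rests on four assumptions: that 470 and 125 are counted by recruitment stream; that the 20% does not already include transfers; that attrition in the control stream is unrelated to diagnosis; and that the CRC stream yields its stated 200 and 100 evaluable cases.

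**What to change.** Either of two changes to Study design and Sample size would do.

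1. Restate the expected evaluable numbers: about 350–357 controls and 219–226 cases in development, and about 93–95 controls and 105–107 cases in validation, with the transfer rule and the 5–7% risk given as the reason. This is wording only and needs no more patients.
2. State that the control targets (470/376 and 125/100) count only patients not found to have CRC, and keep the control stream open until they are met. The stream would then need about 376/(0.8 × 0.95) = 495 to 376/(0.8 × 0.93) = 506 recruits in development and 132–135 in validation. That is 25–36 and 7–10 more patients, and in validation it would exceed the present ceiling of 250.

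Under either option, leave the recruitment of confirmed cases from multidisciplinary meetings at 250 and 125.
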